#### Exclusion criteria

A history of any other neurological condition and/or an inability to provide informed consent. MRI contraindications (eg, pacemakers, stents) will preclude participation in the MRI but not the training part.

#### Intervention

The HD-DRUM app is a computerised version of the drumming training intervention we have previously devised.^19 20^ A detailed description of HD-DRUM according to the Template for Intervention Description and Replication has been published.^21 24^

In brief, the app consists of twenty-two ~10–15 min audio training sessions (figure 2A) that introduce rhythmic patterns of different styles including paradiddles, hip-hop, funk and reggaeton with and without a background metronome or music. Participants will be encouraged to drum along with the audio instructions on two virtual drums (figure 2B) on the tablet screen; with their left hand on a blue triangle and with their right hand on a red circle. The virtual drums produce visual (shrinking) and audio feedback (high and low-pitch bongo sounds) when tapped. The patterns gradually increase in complexity and tempo through the programme. Initially, participants practise with each hand separately before using both hands, starting with one hand first and then reversing the order of the hands. Participants will be asked to complete a training session per day, five times a week, for 8 weeks (40 session in total). They will be able to move through the programme at their own pace and repeat each session as often as they wish. Response time and accuracy will be measured within the app and a success threshold of 60%–70% will need to be achieved to move on to the next level. Researchers will remotely assess training adherence by monitoring coded output files generated and uploaded to a project-specific space on Google Firebase (Google) (https://firebase.google.com) when the tablet is connected to the internet.

**Figure 2 F2:**
[figure not shown]
The HD-DRUM app environment. (A) The app home screen interface that allows users to navigate through and select unlocked training sessions. (B) The virtual drums, a blue triangle (high pitch bongo) and red circle (low-pitch bongo), participants use to tap in synchronisation with the audio instructions.

Participants in the intervention group will be provided with a tablet with the HD-DRUM app installed and an instruction manual for home use. Following completion of baseline assessments participants will receive a face-to-face introduction to the app to familiarise themselves with HD-DRUM. To support retention of the intervention, researchers will maintain weekly contact with participants to provide feedback, assist with any queries or problems and help remove potential barriers. Whenever possible, family members and/or carers will be encouraged to support engagement with the training. Participants will report what support they found helpful in an intervention evaluation questionnaire. Participants in the control condition will be offered the opportunity to borrow a tablet with HD-DRUM to try the training out after they have completed the final assessment of the study.

#### Outcome assessments

##### Primary feasibility outcome assessments

Recruitment will be measured as the number of participants assessed for eligibility, eligible, approached and consented to the study. Reasons for not approaching or enrolling eligible participants will be recorded on a screening log.Retention will be measured by the number of participants who complete the study after attending the follow-up visit after 8 weeks. Reasons for withdrawal and loss to follow-up will be recorded where possible.Acceptability will be measured with a semiquantitative self-report questionnaire on rating how easy the training was to use, how engaging it was, appropriateness of frequency, duration and difficulty, perceived beneficial or detrimental training effects, as well as likes, dislikes and potential improvements within the app. This will inform about any further app adjustments required to address the needs of people with HD for a future RCT.Adherence to the training will be automatically tracked within HD-DRUM by recording the frequency and duration of training sessions.

Feasibility success criteria have been predefined according to the following traffic lights system: green (all feasibility rates ≥70%) will signal that the trial was successful, amber (no rates below 40% but at least one below 70%) that the project requires review and design changes and red (at least one rate <40%) that a future RCT will not be feasible.

##### Secondary outcome measures

Performance in the following measures will be assessed before and after 8 weeks of intervention or usual-activity control (see table 1 for participant timeline).

**Table 1 T1:** Schematic diagram of participant timeline

Assessments for all participants			
	Baseline study visit	HD-DRUM training intervention (completed at home with support and reminders) or control time period	Follow-up study visit
	Day 1	8-week intervention period	End of week 8 (+ 2 weeks)
Cohort Descriptive information			
MOCA*	X		
TOPF	X		
Self-report questionnaire			
Patient Health Questionnaire-8	X		X
HD-DRUM participant evaluation survey			X
Paper and pencil tasks			
Stroop task	X		X
Verbal fluency	X		X
SDMT	X		X
Categorical fluency	X		X
Verbal trails (letter-digit switching)	X		X
Computerised tasks			
N-back Audio (letters)	X		X
N-back Visuospatial (square changing positions in grid)	X		X
N-back dual (audio and visuospatial)	X		X
Flanker task	X		X
Q-Motor assessments			
Speeded finger tapping (left/right index finger)	X		X
Finger metronome tapping (left/right index finger)	X		X
Pointing and tapping (dominant hand)	X		X
Dual (pointing and tapping with dominant hand, speeded finger tapping with opposite hand)	X		X
Speeded foot tapping (left/right)	X		X
Metronome foot tapping (left/right)	X		X
Brain imaging			
T1-weighted MPRAGE	X		X
msHARDI	X		X
qMT	X		X
mcDESPOT	X		X
HD-DRUM group			
HD-DRUM training intervention supported by email and telephone reminders		X	
Control group			
Standard care, usual activities		X	

HD, Huntington’s disease; mcDESPOT, multicomponent-driven equilibrium single pulse observation of T1 and T2; MOCA, Montreal Cognitive Assessment; msHARDI, multi-shell high angular resolution diffusion imaging; qMT, quantitative magnetisation transfer; SDMT, Symbol Digit Modalities Test; T1-MPRAGE, T1-weighted Magnetisation Prepared-Rapid Gradient Echo Sequence; TOPF, test of premorbid functioning

### Cognition, motor function and mood

Participants will undergo the following assessments that have been shown sensitive to cognitive^6^ and motor symptoms in HD.^25 26^ The testing session will take approximately 2 hours including breaks.

Fine motor functions of speeded finger and foot tapping, tapping in synchronisation with and continuation without a metronome, and dual-task motor ability of simultaneously tapping with one hand and pointing with the other will be assessed with the Quantitative Motor (Q-Motor) assessment test battery.^25^ Mean and SD of tapping and pointing speed will be measured in seconds, mean and SD tapping force will be measured in Newtons.Cognitive functions, notably executive abilities of attention switching, distractor suppression and working memory updating^27^ will be assessed with paper-and-pencil and computerised tasks from the Psychology Experiment Building Language (PEBL) test battery^28^ and implemented in MATLAB.^29 30^
Table 2 provides details about all cognitive tasks including their outcome measures and cognitive domain of interest.Mood will be assessed with the brief self-report Patient Health Questionnaire-8.^31^

**Table 2 T2:** Overview of cognitive assessments

Task	Description	Outcome measures	Targeted domain
Background assessment*			
MOCA^45^	Screening of cognitive functions including visuospatial, attention, executive, memory, naming and orientation abilities.	Number of correct responses with a maximum score of 30	Overall cognitive abilities
TOPF-UK^46^	Participants are instructed to read out a list of 70 phonemically irregular words in ascending order of difficulty.	Number of correctly pronounced words.	Premorbid verbal IQ
Working memory updating			
N-back^47^ auditory	Participants are instructed to press a key when an auditory letter stimulus is identical to N trials back (starting with 1-back, 2-back, etc). Participants complete 5 blocks of 20 trials after 1–2 practice sessions. Task difficulty (N-back level) is varied in response to participants’ performance level measured with the sensitivity index A’(^48^) as follows: If A’ > 0.9 then N+1 If 0.75 >A’ > 0.9 then N remains the same If A’ < 0.75 then N-1 (for blocks of N>1) If A’ < 0.65 in two consecutive 1-back blocks, then discontinue	Maximum N-back level attempted,Sensitivity index A’	Phonological working memory maintenance and updating
N-back visuospatial	Participants respond with a key press when the position of a blue square within a 3×3 grid is the same as N trials back under the same task conditions as above.	Maximum N-back level attempted,Sensitivity index A’	Visuospatial working memory maintenance and updating
Dual N-back (auditory and visuospatial)	Participants perform the auditory and visuospatial N-back tasks simultaneously as described above.	Maximum N-back level attempted,Sensitivity index A’	Working memory maintenance and updating,Attention switching, divided attention
Distractor suppression			
Eriksen Flanker^49^	In each trial (160 in total), a target arrow is displayed in the centre of the screen pointing to the left or right. The target is flanked by arrows pointing in the same direction (congruent) or the opposite (incongruent) direction or by horizontal lines (neutral). Participants are instructed to respond to the target direction by pressing either the right or left shift key and ignore the flanker stimuli.	Reaction times in milliseconds,Accuracy rates for congruent, incongruent and neutral conditions	Interference suppression,Target facilitation
Stroop^50^	Participants are presented with a list of 112 colour words printed in incongruent ink colours. First, they are asked to read out the words (baseline), then to name the ink colour for each word (interference) as accurately and fast as they can within a 2 min time limit.	Number of correct responses, time to complete in seconds for baseline and interference conditions	Interference suppression
Attention switching			
Verbal trails^51^	Participants are asked to count 50 digits upwards and recite 50 letters in alphabetical order (starting with A again when reaching Z) (baseline). They are then asked to switch between counting digits and reciting letters from the starting point 28-D and to switch between reciting letters and counting digits from the starting point R-13 for 25 trials each (50 in total) (switching).	Completion time in seconds,ErrorsSwitching cost (switching–baseline)	Attention switching,Divided attention
Cognitive flexibility			
FAS verbal fluency^52^	Participants are asked to generate as many words as they can starting with the letters F, A and S within a time limit of 1 min per letter.	Number of correct words, repetition and intrusion errors.	Cognitive flexibility and fluency
Category Fluency^52^	Participants are asked to generate as many exemplars from the categories ‘animals’ and ‘supermarket items’ as they can within a time limit of 1 min per category.	Number of correct words, repetition and intrusion errors.	Cognitive flexibility and fluency
Processing speed			
SDMT^53^	Participants are asked to match digits to symbols according to a key given to them by filling in rows of blank boxes underneath the target symbols with the corresponding digits within a time limit of 90 s.	Number of correct responses	Psychomotor speed, visuospatial attention, working memory

* oOnly acquired at baseline for cognitive background information.

A’, alpha prime; MOCA, Montreal Cognitive Assessment; SDMT, Symbol Digit Modality Test; TOPF-UK, Test of Premorbid Functioning–UK edition

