## Abstract

**Introduction:**

Huntington’s disease (HD) is an inherited neurodegenerative disease causing progressive cognitive and motor decline, largely due to basal ganglia (BG) atrophy. Rhythmic training offers promise as therapy to counteract BG-regulated deficits. We have developed HD-DRUM, a tablet-based app to enhance movement synchronisation skills and improve cognitive and motor abilities in people with HD. This paper outlines a randomised controlled unblinded trial protocol to determine the feasibility of a larger effectiveness trial for HD-DRUM. Additionally, the trial investigates cognitive and motor function measures, along with brain microstructure, aiming to advance our understanding of the neural mechanisms underlying training effects.

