### Statistical methods

The study will be reported in accordance with the CONSORT statement extension to randomised pilot and feasibility trials.^40^ As this is a feasibility trial, it is not formally powered to test for effectiveness of the intervention while controlling type I error. The primary aim is to assess the feasibility. For this purpose, recruitment, retention and adherence rates and acceptability rating scores and thematic responses will be documented and evaluated according to the success criteria described above. Feasibility percentage rates will be calculated as follows:

Recruitment rate=100×(number of participants consented/number of participants eligible and approached) %.Retention rate=100×(number of participants completing the study at 8-week follow-up/number of participants consented) %.Adherence rate (frequency)=100×(number of days app used for training/40 days) %.Adherence rate (duration)=100×(number of minutes app used for training /(40 days×11.3 min average session duration=451 min) %.

Descriptive summaries such as mean and SD estimates (for continuous variables) of effect sizes and 95% CIs will be calculated for all secondary clinical and MRI outcome measures. Motor and mood measurements are detailed in the outcome section above and information about the cognitive and MRI outcome measures can be found in tables2  3. Differences in mean and SD of participants’ absolute and percentage changes from baseline will be calculated to provide estimates of effect size and variability of any performance changes in the two groups. All calculations will be conducted in SPSS^43^ and R.^41^ This will provide information to help estimate the sample size required for a future definitive RCT into HD-DRUM in this patient population. Note that the absence of a change in individuals with HD in the HD-DRUM group compared with the control group may suggest a beneficial effect of the intervention as HD is a progressive neurodegenerative disease.

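### The listed Q-Motor scores for metronome tapping cannot show better tempo matching or on-beat accuracy, the skill that HD-DRUM trains

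*Protocol article*

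**What the plan says.** The section Cognition, motor function and mood lists speeded finger and foot tapping, "tapping in synchronisation with and continuation without a metronome", and a dual tapping-and-pointing task. Table 1 schedules the metronome tasks in rows of their own, apart from the speeded ones, at baseline and follow-up: "Finger metronome tapping (left/right index finger" and "Metronome foot tapping (left/right" are how those rows begin. They are two of the six Q-Motor rows.

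All these tasks share one scoring rule. "Mean and SD of tapping and pointing speed will be measured in seconds", and "mean and SD tapping force will be measured in Newtons". No tempo error, asynchrony or other deviation from the beat is named.

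Statistical methods does not add to this list. It states that "Motor and mood measurements are detailed in the outcome section above", and that each participant's "absolute and percentage changes from baseline will be calculated" as estimates of effect size and variability, to help size a later definitive trial. The Abstract describes HD-DRUM as "a tablet-based app to enhance movement synchronisation skills".

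**The concern.** A speed score suits tasks in which the participant is asked to go as fast as possible. In a metronome task the participant is asked to match a given interval, and tapping too fast and too slow are both errors. A signed change in the mean interval then does not say whether performance improved.

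These tasks are the motor outcomes closest to what the app trains, and one declared use of the change estimates is planning a larger trial. If the rule is followed as written, a gain in tempo matching or on-beat accuracy would leave no interpretable trace in the between-arm summaries. Statistical methods also remarks that no change in the trained arm relative to control could be a sign of benefit. That reading needs a score with a direction.

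**Working it through.** **Inputs.** The scoring rule, task list and change summaries come from the sections cited above. The document gives no metronome tempo, baseline tempo error or within-trial SD, so there is no stated figure to reproduce. Every timing value below is an assumption for illustration.

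**1. Change in mean interval.** Let T be the metronome interval and m a participant's mean inter-tap interval. Tempo error is |m - T|, which is smallest at m = T. Take T = 0.55 s, half the arm at 0.50 s and half at 0.60 s, and let training halve every error.

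- Fast starters: 0.50 to 0.525 s, change +0.025 s (+5.0%).
- Slow starters: 0.60 to 0.575 s, change -0.025 s (-4.2%).
- Mean change: (+0.025 - 0.025)/2 = 0.000 s. Mean percentage change: (5.0 - 4.2)/2 = +0.4%.
- Mean absolute tempo error: 0.050 to 0.025 s, a fall of 50%.

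If everyone starts at 0.50 s, the same improvement appears as a 5% lengthening of the interval.

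**2. Dependence on the mix of fast and slow starters.** Take an average baseline error of 60 ms, halved by training, with a share p of participants too fast at baseline. The expected change in mean interval is (2p - 1) × 30 ms.

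| Share too fast at baseline | Change in mean interval | Change in absolute deviation |
|---|---|---|
| 0% | -30 ms | -30 ms |
| 25% | -15 ms | -30 ms |
| 50% | 0 ms | -30 ms |
| 75% | +15 ms | -30 ms |
| 100% | +30 ms | -30 ms |

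The true improvement is identical in every row.

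**3. What the SD adds.** If the SD is the within-trial SD of the intervals, smaller means steadier. But adding a constant c to every interval leaves the SD unchanged, so a regular tapper at the wrong tempo scores well. Shifting every tap time by a constant d leaves every interval unchanged, so neither the mean nor the SD of the interval registers a constant lag or lead relative to the beat. Force in Newtons carries no timing information.

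**4. Where the mechanism applies.** A participant averaging 0.50 s against a 0.55 s beat gains 0.05 s per tap and is a full beat out after 0.55/0.05 = 11 taps. That is failure to follow the metronome. Anyone who stays with the beat has a mean interval close to T. Steps 1 and 2 therefore concern mainly continuation tapping. In the paced phase the relevant loss is the one in step 3: on-beat accuracy is not scored.

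**5. Other sources in the plan.** The app records drumming accuracy (Data collection methods), but controls may borrow it only after their final assessment (Intervention). It gives no between-arm comparison.

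**The case against.** The strongest reply is that the rule names the SD as well as the mean. A reader might infer that metronome tapping is judged on mean speed alone, or that the battery is blind to any effect of training. The text does not support either reading: the SD is listed, and if it is within-trial it would register steadier tapping. The article does not say whether it is within-trial. This limits the gap without closing it, as step 3 shows.

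A reader might also infer that the estimate carried to the future trial will be near zero or have the wrong sign. The document does not establish that. It gives no tempo or baseline error, declares no direction of benefit for any motor measure, plans descriptive summaries only, and nowhere makes metronome speed the future primary outcome. Cancelling is possible under assumed values, chiefly in continuation tapping.

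It can be said, too, that a condensed article may leave derived variables to a fuller document, and that tempo deviation can be recovered from each participant's mean once the metronome interval is known. The second point stands and makes the repair cheap. The first carries less weight, because Statistical methods names the outcome section as the place where the motor measures are detailed, and the score given there is the wrong kind for these tasks.

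Finally, the word absolute in the change summaries does not help. Set against percentage, it means change in original units. Even the modulus of a change would treat a move towards the beat and an equal move away from it alike.

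**Conclusion.** The point holds in this form. For metronome finger and foot tapping, change in mean interval has no better or worse direction, and the SD covers regularity at most. The listed motor outcomes therefore cannot show improved tempo matching (mainly continuation) or improved tap-to-beat accuracy (paced phase). The size is illustrative only: under the assumed values, one and the same improvement gives a mean change between -30 and +30 ms.

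Severity is modest. These are secondary, descriptive outcomes in a feasibility trial, the primary feasibility criteria are untouched, and mean speed remains suitable for the speeded and pointing tasks. The change should be made because synchronisation is the trained skill and the change estimates are meant to inform the larger trial.

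**What to change.** For metronome finger and foot tapping, replace change in mean speed by:

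- the absolute deviation of the inter-tap interval from the metronome interval, chiefly for continuation. Take the absolute value for each participant before averaging within an arm; otherwise fast and slow tappers still cancel.
- the absolute tap-to-beat asynchrony in the paced phase, where the recording holds beat times.

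Keep the SD of the interval as the regularity measure and state that it is within-trial. Keep mean speed for the speeded and pointing tasks.

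The cost is a change to the outcome wording and some re-analysis of recordings that the Q-Motor software already captures automatically, with no extra testing. This assumes that tap-level data are kept. If only participant means survive, the deviation of the mean interval can still be computed from the known tempo, but asynchrony cannot.

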#### Inclusion criteria

Individuals over the age of 18 years with a good command of the English language who fulfil the following criteria:

Premanifest or manifest HD as confirmed by genetic testing for the presence of the mutant huntingtin allele.A Unified Huntington’s Disease Rating Scale (UHDRS) TFC^22^ score between 9 and 13.Who participate in the Enroll-HD^23^ observational study (former Registry) (REC no 04/WSE05/89) or in routine clinical assessment of their TFC score.

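### If some participants finish the Stroop list and others are stopped at 2 minutes, neither planned Stroop score alone measures change in everyone; correct responses per second would.

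*Protocol article*

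**What the plan says.** The Stroop row of Table 2 (Cognition, motor function and mood) fixes three things:

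- The material: "Participants are presented with a list of 112 colour words printed in incongruent ink colours".
- The limit: participants first read the words and then name the ink colours "as accurately and fast as they can within a 2 min time limit".
- The scores: the count of correct responses, and "time to complete in seconds for baseline and interference conditions".

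The row does not say what time is recorded for someone who has not finished at 2 minutes, and it defines no score that joins count and time.

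Statistical methods then sets the use of these scores. Means, SDs and 95% CIs "will be calculated for all secondary clinical and MRI outcome measures". For each group, "absolute and percentage changes from baseline will be calculated to provide estimates of effect size and variability". The stated purpose is forward-looking: "This will provide information to help estimate the sample size required for a future definitive RCT into HD-DRUM". Secondary objectives likewise lists variability and change in cognitive tasks as input to future sample-size calculation.

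The eligible range is wide. Inclusion criteria admits "Premanifest or manifest HD as confirmed by genetic testing for the presence of the mutant huntingtin allele", with TFC from 9 to 13.

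**The concern.** A fixed list combined with a time limit bounds both scores. A slow participant is stopped, so the completion time does not exist or is entered as 120 s, and only the count can move. A fast participant runs out of items, so the count is 112 less errors, and only the time can move. Each score therefore carries speed information on one side of a single threshold.

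Other tasks in Table 2 avoid this. SDMT and the fluency tasks are counts in a fixed time, and Verbal trails is a completion time with no stated limit.

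What is at stake is the value of the Stroop estimates for planning. In a sample that mixes finishers and non-finishers, the mean and SD of change in either score depend on how many reach the limit as well as on how much people change. The two scores could also point in different directions for mechanical reasons. Choosing between them afterwards would be a selective choice, in a trial where those collecting the data are unblinded at follow-up (Blinding).

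**Working it through.** The article states no Stroop mean, SD, effect size or finishing rate, so there is no figure of its own to reproduce.

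**Step 1: the threshold, from Table 2 alone.** 112 items / 120 s = 0.933 items per second, or 120/112 = 1.07 s per item. This step needs no assumption beyond the limit applying to the condition in question.

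**Step 2: how much of a true difference in means survives.** Assumptions, none from the article: log-normal naming speed with log-SD 0.25, visit-to-visit noise 5%, accuracy 97%, a 10% gain in speed in the trained arm, and 400,000 simulated participants per arm. Recorded time = min(112/speed, 120). Correct = 0.97 × min(120 × speed, 112).

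| Median speed (items/s) | Finish at baseline | Time keeps | Count keeps |
|---|---|---|---|
| 0.5 | 1% | 1% | 98% |
| 0.6 | 4% | 4% | 90% |
| 0.75 | 20% | 18% | 66% |
| 0.933 | 50% | 47% | 33% |
| 1.1 | 74% | 72% | 14% |
| 1.3 | 90% | 89% | 4% |
| 1.6 | 98% | 98% | 1% |

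Correct responses divided by seconds used (120 s if stopped) keep the full modelled difference at every speed, for example 0.0936 of 0.0936 items/s at the even split.

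**Step 3: standardised effects, since the SD of change moves too.** Assumptions, again not from the article: rate SD 0.25 items/s, correlation between visits 0.85, true gain 0.3 SD, accuracy 95% with random errors. On the true rate, the SD of change is 0.25 × √(2 × (1 − 0.85)) = 0.137 and the gain is 0.3 × 0.25 = 0.075, so d = 0.075/0.137 = 0.55. Random errors lower this to about 0.53 for correct responses per second.

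| Not finishing | d, time cut at 120 s | d, count | d, correct per second |
|---|---|---|---|
| 25% | 0.50 | 0.23 | about 0.53 |
| 50% | 0.43–0.44 | 0.35 | about 0.53 |
| about 80% | 0.30–0.33 | 0.46–0.47 | about 0.53 |

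The matching sample-size ratios are (0.53/d)². At 50% not finishing they are (0.53/0.44)² = 1.5 for time and (0.53/0.35)² = 2.3 for count.

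**Step 4: is the cut-off the cause of the loss in time?** Compare with completion time had there been no limit, at 50% not finishing. If speeds are normal, uncut time gives d of only 0.36 to 0.37, below the cut version, because 112/speed is strongly skewed. If speeds are log-normal, uncut time gives 0.52, so the fall to 0.43–0.44 is due to the limit. The loss in the count is a plain ceiling effect.

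**The case against.** The strongest objection is that the problem is conditional and the article never shows that the condition is met. With 98% finishing, time keeps 98% of the modelled difference; with 1% finishing, the count keeps 98%. A reader might infer that both scores fail whatever the finishing rate, or that the loss grows from TFC 13 to TFC 9 by a known amount. The article supports neither: it has no Stroop speeds, overall or by stage. A mix is plausible given eligibility from premanifest disease to TFC 9, but that is an inference. This objection stands, and the point is worded accordingly.

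Second, the size of the loss in time depends on the model. Under normal speeds, most or all of the shortfall against the rate comes from the skew of a reciprocal and not from the limit. This also stands: the time figures are illustrations, and sample-size ratios built on them should not be read as the effect of the cut-off.

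Third, the rate does well in the simulation partly because rate is what was simulated, and it merges speed with accuracy. That is fair as a caution about HD. It does not touch the structural point that a rate is defined on both sides of 0.933 items per second.

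Fourth, the article does not say that a non-finisher is entered as 120 s, and the limit might apply to ink naming only. A scoring rule may sit in a document not shown, so its absence is no fault. What the article does fix is the pair of scores and the use made of their change.

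Finally, the stakes are small. The Stroop is one of nine repeated cognitive tasks, it is not named as the outcome that will size the next trial, and nothing is lost at data collection. With an assumed 25 per arm, the standard error of d is about √(2/25 + 0.53²/100) = 0.29, larger than the differences between scores shown here. This stands and sets the severity.

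**Conclusion.** The point holds in conditional form. From Table 2 alone, completion time cannot track speed below 0.933 items per second, and above it the correct count shows only errors. If the sample contains both finishers and non-finishers, neither score alone measures change in everyone, and the planned mean and SD of change are distorted as planning inputs.

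The size cannot be fixed from the article. Under the stated assumptions an even split gives d of 0.43–0.44 for time and 0.35 for count, against about 0.53 for the rate. The weaker score changes from time to count as more people finish. The time figures rest partly on the shape assumed for naming speed.

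It would go too far to say that the trial's estimates will be biased by a given factor or that the Stroop is unusable: count and time together do cover the whole range, and only a score that joins them is lacking. The primary feasibility criteria are untouched. Severity is low; this is a cheap improvement to one descriptive secondary outcome.

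**What to change.** In Table 2 or the analysis plan, add for each condition (word reading and ink naming) correct responses per second of time used, where time used is the time to finish or 120 s if stopped. Make this the main Stroop score for change and for sample-size estimates. Keep count and time as descriptive scores, and report per arm, visit and condition how many were stopped at the limit. State in the same place whether the limit covers both conditions.

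The cost is a line or two of text: both components are already recorded and no assessment changes. The small downside is that a rate merges speed and accuracy, so errors should still be shown separately. Fixing the score before the follow-up data are examined also removes the later choice between count and time.
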